# Effect of a low-FODMAP diet for the management of functional abdominal pain disorders in children: a study protocol for a randomized controlled trial

**DOI:** 10.1186/s12937-020-00656-3

**Published:** 2021-01-02

**Keywords:** Child, Functional abdominal pain disorders, Irritable bowel syndrome, Diet, RCT

## Abstract

**Background:**

Evidence from studies in adults documents that fermentable oligosaccharides, disaccharides, monosaccharides, and polyols (FODMAPs) may be triggers of symptoms in individuals with functional abdominal pain disorders (FAPDs). However, in children, the evidence is very limited. We aim to assess the effects of a low-FODMAP diet compared with a regular diet for the management of children with FAPDs.

**Methods:**

We will perform a randomized, quadruple-blinded, controlled trial. Seventy-four children aged 8 to 18 years with a FAPD (Irritable Bowel Syndrome or Functional Abdominal Pain-Not Otherwise Specified), diagnosed according to the Rome IV criteria, will be randomly allocated to receive either a low-FODMAP diet or a regular diet for 4 weeks. The primary outcome will be the percentage of the responders, defined as the participants who have at least 30% improvement in abdominal pain intensity on a Visual Analogue Scale (VAS) during the last week of the trial compared with baseline, that is at least equal to the Reliable Change Index (≥ 25 mm change on VAS). Other outcomes will include changes in stool consistency, abdominal pain frequency, total scores on the Gastrointestinal Symptom Rating Scale, KIDSCREEN-10 Index and World Health Organization Five Well-Being Index, child’s school attendance and parents’ work absenteeism, and BMI-for-age z-score. Compliance, tolerability of the low-FODMAP diet, and adverse events also will be evaluated. Each FAPD subtype will be assessed separately.

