#### Sample size

The primary outcome is the reduction in the abdominal pain intensity in the low-FODMAP diet group compared with the regular diet group over the 4-week intervention. We assumed a 30% difference as being a clinically significant primary endpoint [16]. We estimate that 31 children in each group are needed to achieve a significant difference with a power of 80%, along with a two-sided 5% significance level. Given the anticipated dropout rate of 20%, we estimate 37 subjects are necessary in each study arm. Sample size calculations were performed with StatsDirect (StatsDirect Ltd. StatsDirect statistical software. http://www.statsdirect.com. England: StatsDirect Ltd. 2013).

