### Assignment of interventions

#### Sequence generation and allocation concealment

Randomization will be based on a computer-generated randomization list developed by an independent investigator with no clinical involvement in the trial. The random numbers will be generated in blocked randomization (using a random block of 4: 2 subjects in group A and 2 in group B) with a 1:1 allocation ratio to ensure good balance between participant characteristics in both groups. The randomization sequence will be created using StatsDirect statistical software. Stratification will not be performed.

Allocation concealment will be ensured using opaque, sealed, numbered envelopes. The data regarding intervention assignments will be stored in a sealed envelope in a safe in the administrative part of the department. An independent person will open the next consecutively number envelope. Information about allocation of each participant will be given to the dietitian. The dietitian will develop a meal plan for each enrolled participant following the allocation. Each meal plan will contain the full name and address of the child. The meal plans will be provided to the catering company. The catering company will not be informed about the type of diet, and no suggestive information will be attached to the all-day box-diet provided to the participant.

After performing the data analysis, code numbers will be opened by the research coordinator (AH). In case any medical problem occurs for which treatment allocation is needed, the code can be broken by a principal researcher (AH, HS).

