#### Data analysis

All analyses will be conducted on an intention-to-treat basis, including all patients in the groups to which they are randomized for whom outcomes are available (including dropout and withdrawals). Per-protocol analysis also will be performed, in which all subjects who finish the study according to the protocol will be included.

Descriptive statistics will be used to summarize baseline characteristics. The Student t-test will be used to compare mean values of continuous variables approximating a normal distribution. For non-normally distributed variables, the Mann-Whitney U test will be used. The x^2^ test or Fisher exact test will be used, as appropriate, to compare percentages. The same computer software will be used to calculate the relative risk (RR), number needed to treat (NNT), and mean difference (MD), all with a 95% confidence interval (CI). The difference between study groups will be considered significant when the *p* value is < 0.05, when the 95% CI for RR does not include 1.0, or when 95% CI for MD does not include 0. All statistical tests will be two-tailed and performed at the 5% level of significance.

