#### Methods of additional analyses

Both the primary and secondary outcomes will be analyzed by logistic regression, controlling for three, prespecified, potential confounding variables, i.e., age, sex, and subtype of IBS. The difference between study groups will be considered significant when the *p* value is < 0.05, when the 95% CI for RR (or odds ratio [OR]) does not include 1.0, or when 95% CI for MD does not include 0. All statistical tests will be two-tailed and performed at the 5% level of significance.

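### FAPD subtypes are to be assessed separately under a blanket 5% rule, yet the trial is sized only for the pooled comparison and its one model neither separates IBS from FAP-NOS nor tests for a different effect

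*Protocol article*

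**What the plan says.** Five places in the protocol article bear on this point.

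- **Abstract, Methods.** The list of outcomes closes with "Each FAPD subtype will be assessed separately". Nothing there marks this as exploratory or descriptive.
- **Data analysis.** After listing the t-test, Mann-Whitney, chi-square and Fisher tests, the section sets one rule for everything: "All statistical tests will be two-tailed and performed at the 5% level of significance". Methods of additional analyses repeats the rule.
- **Methods of additional analyses.** The only model is a logistic regression "controlling for three, prespecified, potential confounding variables, i.e., age, sex, and subtype of IBS".
- **Sample size.** "We estimate that 31 children in each group are needed", "with a power of 80%, along with a two-sided 5% significance level". Then: "Given the anticipated dropout rate of 20%, we estimate 37 subjects are necessary in each study arm". The calculation concerns the two diets in the whole trial.
- **Sequence generation and allocation concealment.** "Stratification will not be performed".

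The inclusion criteria admit two diagnoses, IBS and FAP-NOS. They divide IBS further by stool consistency into IBS-D and IBS-C. The expected share of each diagnosis is not given.

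**The concern.** Two separate tests, one in each diagnosis, do not answer whether the diet works differently in IBS and in FAP-NOS. Each uses only part of a sample that was just large enough for the pooled question. If the effect is real and equal, it is therefore common for one test to reach significance and the other to miss it. The model does not repair this. A main effect for subtype adjusts the overall comparison but says nothing about a difference in effect. Its label also follows the IBS-D/IBS-C language of the inclusion criteria rather than the split between the two enrolled diagnoses, so the abstract and the model do not fit each other.

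The Abstract and the Discussion say that the findings should inform guidelines. A result that is significant in one diagnosis only could be read as evidence that the diet suits that diagnosis and not the other, although no comparison between them had been made.

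**Working it through.** **1. The plan's own figure.** The Sample size section says "We assumed a 30% difference as being a clinically significant primary endpoint" and gives no control rate or SD. I read the 30% as 30 percentage points of responders. The pooled-variance formula for two proportions at 80% power and two-sided 5% gives, per arm:

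- 29 for 7% vs 37%
- 32 for 10% vs 40%
- 39 for 20% vs 50%
- 42 for 30% vs 60%

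So 31 fits a control rate of about 7 to 10% (or the mirror image, about 60% vs 90%). It also fits a standardised difference of 0.72. It cannot be traced to a single input. The step to 37 matches 31 × 1.2 = 37.2. Nothing in the calculation refers to a subtype.

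**2. Assumptions (none is in the protocol).** An even split gives 31/2 = 15.5 to 37/2 = 18.5 children per arm in each diagnosis, taken as 15 and 18. Control response is 10, 20 or 30%, with the same 30-point gain in both diagnoses.

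**3. Formulas.** For one diagnosis with n per arm, the exact rejection probability P sums the two binomial probabilities over all tables with p < 0.05. Chi-square (uncorrected) and Fisher are both shown, because the plan allows either. The diagnoses are independent, so:

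- exactly one significant = 2P(1 − P)
- both significant = P²
- with no effect and actual size a, at least one false positive = 1 − (1 − a)²

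Example, 30% vs 60%, n = 18, chi-square: P = 0.493; 2 × 0.493 × 0.507 = 0.500; 0.493² = 0.243.

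| Control vs diet | n per arm | Test | P | Exactly one | Both | No effect (control rate in both arms): at least one |
|---|---|---|---|---|---|---|
| 10 vs 40% | 15 | chi-square | 51.0% | 50.0% | 26.0% | 5% |
| | 15 | Fisher | 32.5% | 43.9% | 10.6% | 1% |
| | 18 | chi-square | 56.1% | 49.2% | 31.5% | 7% |
| | 18 | Fisher | 42.6% | 48.9% | 18.1% | 2% |
| 20 vs 50% | 15 | chi-square | 41.9% | 48.7% | 17.5% | 10% |
| | 15 | Fisher | 24.6% | 37.1% | 6.0% | 3% |
| | 18 | chi-square | 49.8% | 50.0% | 24.8% | 9% |
| | 18 | Fisher | 35.9% | 46.0% | 12.9% | 4% |
| 30 vs 60% | 15 | chi-square | 37.0% | 46.6% | 13.7% | 11% |
| | 15 | Fisher | 22.7% | 35.1% | 5.2% | 3% |
| | 18 | chi-square | 49.3% | 50.0% | 24.3% | 10% |
| | 18 | Fisher | 35.6% | 45.8% | 12.7% | 4% |

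Exactly one is significant in 35 to 50% and both in 5 to 32%. At the nominal 5% per test, the no-effect figure would be 1 − 0.95² = 9.75%.

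**4. Uneven splits.** To avoid choosing response rates, set the effect so that the pooled test has 80% power at 31 per arm: d = (1.96 + 0.8416) × √(2/31) = 0.712 SD. By normal approximation, exactly one diagnosis is then significant in 50% of trials for a 50:50 split, 53% for 65:35 and 61% for 80:20. With all 37 per arm the figures are 49%, 52% and 63%.

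**5. What an interaction test can do.** Suppose the full effect d exists in one diagnosis and none in the other, with a and b children per arm in the two diagnoses. Power is Φ(d/√(2/a + 2/b) − 1.96). With a = b = 15.5 this is Φ(0.712/0.508 − 1.96) = Φ(−0.56) = 29%. Over the splits and totals in step 4 it runs from 20 to 33%.

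**The case against.** The strongest reply is that the abstract says assessed, not tested. Estimates with intervals in each diagnosis would satisfy that word, and Data analysis already promises 95% CIs. The hypothesis and the sample size are pooled, and no section says that subtype conclusions will rest on one p-value set against another. This stands. A reader might infer that the trial plans to declare the diet effective in one diagnosis only, or is likely to do so. The document supports neither. Step 3 applies only if a real and equal effect exists, and the misreading would still have to be made by someone. With Fisher's test, neither diagnosis significant is often the commonest result.

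A second reply is that an interaction test may be in a fuller plan that is not shown. That also stands, so its absence is not the point here. The point rests on what is printed: an unqualified promise of separate assessment, a significance rule without exceptions, and a covariate that does not match the two diagnoses.

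Two further inferences should be resisted. One is to multiply the error over four subtypes: only two of the Rome IV diagnoses are enrolled, and IBS-D and IBS-C lie within IBS, so four independent tests have no basis. The other is that unstratified allocation invalidates comparisons within a diagnosis. It only leaves balance there to chance.

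Finally, an interaction test with 20 to 33% power settles little. That is true, and it is why the subtype results should be exploratory.

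**Conclusion.** The point holds as a mismatch with a practical consequence. The abstract commits to separate assessment, the only stated decision rule is 5% for every test, the sample supports the pooled comparison alone, and the one model neither defines IBS versus FAP-NOS nor tests for a different effect. If the effect is equal in both diagnoses, significance in exactly one would appear in about 35 to 50% of trials with an even split, and somewhat more often with an uneven one (up to about 63% in step 4). Both would be significant in about 5 to 32%. With no effect, at least one false positive arises in about 3 to 11% at response rates of 20 to 30%, and in about 1 to 7% at 10%. The split, the response rates and the equal effect are assumptions. The primary pooled analysis is not affected.

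**What to change.** Bring the abstract and Methods of additional analyses into line:

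1. Define the covariate as diagnosis, IBS versus FAP-NOS. If IBS-D and IBS-C are also wanted, name them as a separate description within IBS.
2. Add one treatment-by-diagnosis interaction to the adjusted model for the primary outcome, and name its scale.
3. Report the effect in each diagnosis and the interaction, each with a 95% CI, label them exploratory, and exempt them from the blanket 5% rule so that no separate significance claim is made for a diagnosis.
4. State that a non-significant interaction will not be taken as evidence of equal effects.

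The cost is one model term and a few sentences, with no extra children and no change to the primary test. The trial gives up stand-alone claims for either diagnosis, and the interaction estimate will be imprecise, the more so if one diagnosis is rare.

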**Discussion:**

There is a need for high-quality evidence regarding the dietary management of children with FAPDs. This randomized controlled trial (RCT) of rigorous methodological design will help to establish the effectiveness, if any, of a low-FODMAP diet for the management of FAPDs in the pediatric population. The findings of this RCT will assist with the development of guidelines and influence the direction of further research.

**Trial registration:**

NCT04528914

**Data and protocol version identifier:** 24/08/2020

**Supplementary Information:**

The online version contains supplementary material available at 10.1186/s12937-020-00656-3.

## Background

Functional abdominal pain disorders (FAPDs) affect 13.5% of children worldwide [1]. The Rome IV Criteria distinguished four types of FAPD: irritable bowel syndrome (IBS) (the most common, 8.8, 95% confidence interval [CI] 6.2–11.9) [1], abdominal migraine, functional dyspepsia, and functional abdominal pain – not otherwise specified (FAP-NOS) [2]. The main symptom of each is chronic abdominal pain which cannot be fully explained by any other medical condition. The diagnosis is symptom-based; however, it should be preceded by the exclusion of other diseases (e.g., celiac disease), especially if alarming symptoms occur.

The mechanisms underlying FAPDs are complex. Among them is a brain-gut axis disorder, resulting from the interaction of genetic, environmental, and psychological factors [2–4]. As the impact of FAPDs on school absenteeism, hospital admissions, psychosocial functioning of children, absenteeism of caregivers, and cost for families and healthcare providers is substantial [3–5], there is a need for evidence-based therapeutic options.

Whereas evidence from studies in adults suggests that fermentable oligosaccharides, disaccharides, monosaccharides, and polyols (FODMAPs) may be triggers of symptoms in individuals with FAPDs, evidence in children is very limited. However, a low-FODMAP diet is commonly prescribed for IBS in both adults and children, despite the limited evidence of its effectiveness [3]. The rationale for the aforementioned dietary restrictions is based on the assumption that a decrease in the short-chain fermentable carbohydrate load both prevents the osmotic effect of FODMAPs, resulting in a decrease in small intestine water volume, and limits the exaggerated fermentation of FODMAPs by colonic microbiota and associated gas production, which may alleviate the chronic abdominal pain [6, 7]. The FODMAPs are poorly absorbed in healthy people as well as in patients with FAPDs; however, a high intake of FODMAPs is associated with gastrointestinal symptoms only in the latter population, which is explained by the presence of visceral hypersensitivity and altered gut motility [8].

A 2017 updated Cochrane systematic review [3] found only one short-term (2 days), double-blind, cross-over, randomized controlled trial (RCT) investigating use of a low-FODMAP diet in children with IBS (*n* = 33) [9]. The authors reported fewer episodes of abdominal pain per day and no adverse events after 2 days of a low-FODMAP diet compared with both a traditional American childhood diet and the baseline value. Pain intensity improvement was reported for 8 responders and 10 placebo responders. For dietary modification of a single FODMAP, the evidence is also limited. A 2015 systematic review [10] found no effect of a lactose-free diet in children with recurrent abdominal pain (two RCTs). In both systematic reviews (Rutten [10] and Cochrane 2017 [3]), limited evidence was reported for a fructose-restricted diet (one RCT). A 2017 systematic review [11], which assessed the methodological quality of RCTs investigating use of a low-FODMAP diet in an age-mixed population with IBS, concluded that all included studies had domains with a high risk of bias. The short study duration, difficulties with blinding of study participants, and problems with selection of the control group were reported as the main study limitations. Further studies are needed, especially in children, which will address these limitations and determine the effectiveness of use of a low-FODMAP diet in children with FAPDs including IBS and FAP-NOS.

## Methods

This study was designed in accordance with Consolidated Standards of Reporting Trials (CONSORT) 2010 [12] and Standard Protocol Items: Recommendations for Interventional Trials (SPIRIT) 2013 [13] Statements (see Additional file 1). Additionally, the design of this study follows the guidelines of the Rome Foundation Working Group [14, 15], and pediatric subcommittee [16], as well as a core outcome set for clinical trials in pediatric FAPDs [17].

### Study objective and hypothesis

The primary aim of this RCT is to test the hypothesis that children with IBS and FAP-NOS who receive a low-FODMAP diet will have a lower mean abdominal pain intensity score compared with those who receive a regular diet after 4 weeks of intervention.

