#### Outcomes

In agreement with recommendations [16], one primary outcome was pre-specified:
**Change in abdominal pain intensity.** Responders will be those with a daily reduction in the intensity of abdominal pain episodes of at least 30% at week 4 compared with baseline, and this value should be at least equal to the Reliable Change Index (RCI) for that sample [16, 27]. A cut-off of 25 mm for RCI change was adopted [16]. This outcome also will be assessed as the change at weeks 1, 2, and 3 from baseline.

For participant timeline, see Table 1.

Secondary outcomes to be assessed during the 4-week intervention, following the standardized core outcome set [17], will be:

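### The primary hypothesis is about mean pain, the primary outcome is a responder percentage, and no section says which comparison decides the trial

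*Protocol article*

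**What the plan says.** Four places in the protocol article describe the primary question.

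- **Study objective and hypothesis:** the primary aim is to test whether the low-FODMAP group "will have a lower mean abdominal pain intensity score compared with those who receive a regular diet after 4 weeks of intervention". This is a comparison of means.
- **Abstract, Methods:** "The primary outcome will be the percentage of the responders, defined as the participants who have at least 30% improvement in abdominal pain intensity", with the further condition of at least 25 mm on the VAS. This is a comparison of percentages.
- **Outcomes:** a single pre-specified primary outcome, introduced as "Change in abdominal pain intensity. Responders will be those with a daily reduction" of at least 30% at week 4, again with a 25 mm cut-off. The title is a change in intensity and the definition is a responder.
- **Sample size:** "The primary outcome is the reduction in the abdominal pain intensity in the low-FODMAP diet group" compared with the regular diet group. The assumed effect is a 30% difference, giving 31 per arm at 80% power and two-sided 5%. No responder rate and no standard deviation are given.

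The Data analysis section lists t-test or Mann-Whitney for continuous variables and chi-square or Fisher for percentages. It adds RR, NNT and MD, and reads a difference as significant when p < 0.05, "when the 95% CI for RR does not include 1.0, or when 95% CI for MD does not include 0". Methods of additional analyses repeats that sentence. Neither section links a test or effect measure to the primary outcome.

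**The concern.** A lower mean score and a higher responder percentage are different claims about the same VAS data. The first is tested by a t-test and reported as an MD; the second is tested by chi-square or Fisher and reported as an RR. The responder definition has two thresholds, one relative and one absolute, so the percentage and the mean need not move together in a trial of this size.

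If the two analyses disagree, the hypothesis section supports one verdict and the abstract and Outcomes section support the other. A choice made after unblinding could not be shown to be independent of the data. If both were open, the primary claim would no longer carry a 5% error rate.

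**Working it through.** **1. Does the stated sample size show which scale was meant?** The inputs from Sample size are 80% power, two-sided 5%, a 30% difference and n = 31 per arm.

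*As proportions.* With p̄ the average of p1 and p2, n = [1.960·√(2p̄(1−p̄)) + 0.842·√(p1(1−p1) + p2(1−p2))]² / 0.30², without continuity correction. Power at n = 31 is Φ{[0.30·√31 − 1.960·√(2p̄(1−p̄))] / √(p1(1−p1) + p2(1−p2))}. The control rates are assumptions.

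| Control vs low-FODMAP | n per arm, 80% power | Power at 31 per arm |
|---|---|---|
| 10% vs 40% | 31.5, so 32 | 79% |
| 20% vs 50% | 38.5, so 39 | 71% |
| 30% vs 60% | 42.0, so 42 | 67% |
| 35% vs 65% | 42.4, so 43 | 66% |
| 40% vs 70% | 42.0, so 42 | 67% |
| 50% vs 80% | 38.5, so 39 | 71% |
| 60% vs 90% | 31.5, so 32 | 79% |

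*As means.* n = 2(1.960 + 0.842)²/d², so n = 31 needs d = 2.802·√(2/31) = 0.71. That is, for example, 30 mm with an SD of about 42 mm, or 25 mm with an SD of about 35 mm.

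So 31 can be approached on either scale, but only by supplying an input that the protocol does not give. The sample size does not identify the primary endpoint.

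**2. Type I error if either test could be claimed.** Two tests at 5% give 1 − 0.95² = 9.75% if independent, and at most 0.05 + 0.05 = 10% under any dependence. The two measures are correlated, so I rely on null simulation with 40,000 trials per setting and 31 or 37 per arm. The assumptions, none from the documents, are:

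- baseline VAS of mean 55 and SD 15, with values below 30 set to 30;
- the same fall of 5, 15 or 25 mm in both arms;
- residual SD of 15, 22 or 28 mm.

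Responders are defined as in the protocol, and the t-test is on week-4 VAS or on change, one at a time.

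- t-test or chi-square: 7.3% to 10.0%.
- t-test or Fisher: 5.5% to 7.1%. Fisher alone runs well below 5% at this size.

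**3. How often the two tests disagree when the diet works.** Same model, 31 per arm, residual SD 22 mm, t-test on week-4 VAS against uncorrected chi-square, 20,000 trials per row.

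| Fall on regular diet | Extra fall on low-FODMAP | Responders, regular vs low-FODMAP | t-test significant | Chi-square significant | Exactly one significant |
|---|---|---|---|---|---|
| 5 mm | 10 mm | 18% vs 33% | 31.5% | 25.7% | 24.9% |
| 5 mm | 12 mm | 18% vs 36% | 41.8% | 34.6% | 27.5% |
| 5 mm | 15 mm | 18% vs 41% | 59.3% | 51.2% | 28.5% |
| 15 mm | 10 mm | 32% vs 50% | 30.6% | 29.9% | 22.8% |
| 15 mm | 12 mm | 32% vs 54% | 41.4% | 41.0% | 25.7% |
| 15 mm | 15 mm | 32% vs 59% | 58.3% | 58.1% | 25.9% |

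In about a quarter of such trials the verdict depends on which section is followed.

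**The case against.** Most of the text favours responders. The abstract says so outright, and the Outcomes section, which governs, declares one primary outcome and gives only a responder definition. The planned logistic regression of the primary outcome also suits a binary variable, although the same sentence applies it to all secondary outcomes, several of them continuous. Only the hypothesis speaks of a mean, and the sample-size wording can be read either way. This stands, and it is why the fix can follow the responder definition. It does not remove the conflict, because a responder percentage does not test a hypothesis about a mean score.

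A reader might infer from the RR-or-MD sentence that the plan adopts a rule under which the primary claim succeeds if either interval excludes the null. The documents do not support that. The sentence follows a list of tests for all outcomes and reads most naturally as a general convention: RR for percentages, MD for continuous measures. The difficulty is only that it cannot settle a scale that other sections leave in conflict.

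A reader might also count a t-test on change as a third route and quote an error of 11% to 13%, as simulated with assumed baseline-to-week-4 correlations of 0.3 to 0.7. No section makes those three tests alternative primary analyses.

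Finally, a journal article may leave test details to a fuller document. That would excuse silence. It does not excuse two statements of the primary question that differ, since an analysis plan could not tell which to implement.

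**Conclusion.** The inconsistency is real and lies in the text: the hypothesis concerns a mean, the single primary outcome is a responder percentage, and the sample size rests on a 30% difference of unstated scale. Nothing says which comparison is confirmatory.

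The error inflation is moderate and conditional. It is about 5.5% to 10%, depending on the test for percentages and on assumed pain distributions, and it arises only if either result may be claimed as primary, which the protocol never says. The larger practical risk is disagreement between the two analyses, at 23% to 29% of trials under an assumed true benefit of 10 to 15 mm. The ambiguity can therefore change the trial's conclusion and should be settled before unblinding.

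**What to change.** In Study objective and hypothesis, Outcomes, Sample size and Data analysis, state one confirmatory test: the difference in responder proportion at week 4, low-FODMAP versus regular diet, two-sided 5%, with chi-square or Fisher chosen in advance. This agrees with the abstract and the responder definition already in Outcomes. Reword the hypothesis to match, list the difference in mean VAS at week 4 as a secondary outcome, and add that the primary claim rests on the responder test only. The RR/MD sentence can stay as a general convention.

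The Sample size section must then give the assumed responder rate in each arm. This is where the cost lies. Unless the control rate is near 10% or 60%, the stated 80% power for a 30-point difference has to be restated, to about 66% to 71% at 31 per arm for control rates of 20% to 50%. Even with all 37 per arm analysed, power in that range is 74% to 78%. Keeping 80% would need 39 to 43 per arm before dropout, and more with Fisher or a continuity correction (45 for 20% vs 50% with the correction). Otherwise the change is wording, although the protocol requires a formal, ethics-approved amendment for changes that may affect design or sample size.
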